### Randomization

Health facilities were randomly allocated into one of the three study arms, resulting in 28 facilities per study arm. The randomization of clusters was performed by an independent epidemiologist not directly involved in the research project using a pseudorandom number sequence generated using Excel (Microsoft). Owing to the nature of the intervention, blinding of study participants and data collectors is not possible; however, outcome data will be collected by independent data collectors not involved in the intervention delivery. The study setting (Figure 1), recruitment strategies, random allocation sequence, intervention implementation, and data collection points (Figure 2) are summarized below.

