## Methods

### Study Setting

The study will be conducted in 4 districts in the Koulikoro region, Mali. The study area was selected as it is part of a larger project implemented by the Canadian Red Cross in collaboration with the Malian Red Cross (Croix-Rouge Malienne). This project is an integrated 4-year (2016-2020) maternal neonatal and child health (MNCH) intervention that targets 6 districts across the Koulikoro and Sikasso regions and is funded by the Government of Canada. The project supports the primary and secondary health facilities (CSCOMs and Centre de Santé de Référence [CSREF]—referral health centers) to improve the quality of their MNCH services and strengthen the health management information system. At the community level, the Malian Red Cross has a strong presence because of the training and support of local community health workers and volunteers for MNCH-related activities at remote integrated management of childhood illness sites.

The Koulikoro region is the second-most-western region of Mali. It covers an area of 90,120 square kilometers. With an estimated population in 2017 of 3.1 million and a density of 26.8 people per square kilometer. The Koulikoro region is separated into 7 districts: Kati, Kangaba, Koulikoro, Kolokani, Nara, Banamba, and Dioïla. The Canadian Red Cross and Malian Red Cross program encompasses the latter five. Of these, 4 districts (Koulikoro, Kolokani, Banamba, and Dioïla) will be included in this study.

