### Cluster Size and Selection

Community health facilities, including community health workers serving the catchment area, are the units of randomization (clusters). Although there are some differences in the services provided at these facilities according to the baseline facility assessment conducted in December 2016, only those health facilities providing basic obstetric care with at least one health care provider trained in the active management of the third stage of labor (AMTSL), essential newborn care (ENC), perinatal care (PNC), and those who had not yet started implementing the audits are considered for inclusion in the study. All facility deliveries (both mother and newborn) within study clusters and live home births referred to a facility within the perinatal period are included in the trial, subject to informed consent. In that respect, a master list of 84 facilities meeting the inclusion criteria within the 4 districts will be generated.

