### Sample Size

A sample size of 600 births per cluster was calculated to have 80% power to detect a reduction in the perinatal mortality rate from 30% to 27% live births, which corresponds to a 10% reduction in the perinatal mortality rate between intervention and control arms (α=5%, intracluster correlation of 0.003, and coefficient of variation of cluster size 0.9 and a 0.96 correlation of baseline measures with outcome). The number of clusters available per arm was 28. The expected average number of deliveries per month in each cluster was approximately 38, resulting in 16 months of follow-up. Two additional months of data collection are planned to account for losses and refusals and allow for adjustments in the analysis, resulting in a final average cluster size of approximately 675 births over 18 months.

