## Results

The trial is completed. The recruitment began on July 15, 2019, and data collection began on July 23, 2019, and was completed in November 2020. Data cleaning or analyses began at the time of submission of the protocol. As the randomization is performed at the health facility level, we will undertake aggregate cluster-level analysis comparing the proportion between treatment arms [30]. We will compare differences in the proportion of perinatal mortality between intervention and control groups using a chi-square statistic adjusted for the effect of clustering within health facilities [31] using a formula that incorporates the intraclass correlation coefficient as a measure of the extent of clustering [32].

The analysis and report of the intervention effect will be carried out in accordance with CONSORT (Consolidated Standards of Reporting Trials) principles and its extension for pragmatic trials [33].

We will perform all analyses using Stata version 16.1 software (Stata Corp).

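### The stated primary test has no place for district or delivery volume, although both appear to be known for each facility, so precision may be lost

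*Protocol article*

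**What the plan says.** - **Allocation.** Under Randomization, an independent epidemiologist allocated facilities "using a pseudorandom number sequence generated using Excel", "resulting in 28 facilities per study arm". The text mentions no stratification, matching or other restriction.
- **District.** Study Setting states: "The study will be conducted in 4 districts in the Koulikoro region, Mali". Cluster Size and Selection adds that "a master list of 84 facilities meeting the inclusion criteria within the 4 districts will be generated". District membership was therefore known for every facility at allocation.
- **Volume.** Sample Size states: "The expected average number of deliveries per month in each cluster was approximately 38". It also uses a "coefficient of variation of cluster size 0.9". Both figures imply some knowledge of volumes across facilities at design.
- **Analysis.** The analysis paragraph under Results compares proportions at cluster level with a chi-square "adjusted for the effect of clustering within health facilities", using a formula built on the intraclass correlation. No district, volume or baseline term appears.
- **Adjustment foreseen.** Sample Size adds two months of data collection, partly to leave room for adjusted analysis, but names no covariates.

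**The concern.** With few events per facility and a small target difference, much of the uncertainty in a cluster trial comes from true differences between facilities. A regression can remove whatever part of that is explained by variables known before the trial. The chi-square stated here only widens the standard error to allow for clustering. It has nowhere to put district or volume.

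Two things are at stake. One is precision, if these variables predict perinatal mortality. The other is credibility: if one arm happened to draw busier facilities or a different mix of districts, the stated primary result would not take account of it.

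**Working it through.** **Inputs (Sample Size section):** 28 facilities per arm; m = 600 births per facility; intraclass correlation (ICC) 0.003; cluster-size CV 0.9; baseline-outcome correlation 0.96; alpha 5% (two-sided assumed); printed rates 30% and 27%. The Primary Outcome section defines the outcome per 1000 live births.

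**1. The plan's own power.** The plan states: "A sample size of 600 births per cluster was calculated to have 80% power".
- Design effect = 1 + ((0.9² + 1) × 600 − 1) × 0.003 = 1 + 1085 × 0.003 = 4.255.
- With the baseline term, effective n per arm = 28 × 600 / (4.255 × (1 − 0.96²)). At 30 versus 27 per 1000, power is 81.6%, which reproduces the stated figure.
- Read literally as 30% versus 27%, power is 84.0% without the baseline term and about 100% with it. The per-1000 reading matches the outcome definition and uses all the listed inputs, so it is used below.
- At 30 versus 27 per 1000 without the baseline term, power is 12.3%.

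**2. Between-facility variation, per-1000 reading.**
- SD of true facility rates = √(0.003 × 0.03 × 0.97) = 0.00934, or 9.3 per 1000.
- Between-facility part of the SE of an arm difference, equal clusters: 9.34 × √(2/28) = 2.5 per 1000.
- With CV 0.9: 2.50 × √(1 + 0.81) = 3.4 per 1000.
- Target difference: 3 per 1000.

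**3. Share of the variance of the arm difference,** with 30 per 1000 in both arms.
- Within-facility part: 2 × 0.03 × 0.97 × 0.997 / 16,800 = 3.45 × 10⁻⁶.
- Equal clusters: between part 6.24 × 10⁻⁶; share 6.24 / 9.69 = 64%.
- CV 0.9: between part 11.29 × 10⁻⁶; share 11.29 / 14.74 = 77%.

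**4. Possible gain from adjustment.** If district and volume explain a proportion R² of the between-facility part, the SE is multiplied by √(1 − share × R²). R² is an assumption, because the documents give no figure.

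| R² | Fall in SE, share 64% | Fall in SE, share 77% |
|---|---|---|
| 10% | 3% | 4% |
| 25% | 8% | 10% |
| 50% | 18% | 21% |

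Power at CV 0.9 with no baseline term rises from 12.3% to 13.0% (R² = 10%), 14.7% (30%) or 17.3% (50%). Removing all between-facility variance would give 37.9%.

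**5. Chance imbalance if allocation was unrestricted (simulation).**
- Volumes with CV 0.9: two given arms differ in total births by more than 25% in about 35% of allocations. With lognormal volumes the ratio has median 1.17 and 90th percentile 1.48.
- Assuming 21 facilities per district: two given arms differ by 6 or more facilities in some district in 28% of allocations. For any pair of the three arms the figure is 54%.

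These figures describe imbalance in births and facility counts, not in mortality.

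**The case against.** A reader might infer that facilities were definitely allocated without regard to district or volume, that the comparison is therefore distorted, and that facility variation swamps the target effect. The documents do not support this.

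- **Allocation.** The quoted words say how the number sequence was made and do not exclude strata. The article is condensed, and the flow chart it points to is not shown. It is fair to say only that no restriction is described.
- **Validity.** Unrestricted allocation of 28 facilities per arm is legitimate. The ICC and the size CV enter the sample size, and the ICC enters the test. The 2.5 to 3.4 per 1000 is already inside the standard error and is not a further threat. There is no bias.
- **Size.** Calling the variation overwhelming depends on the per-1000 reading. On the literal percentages, the facility SD is √(0.003 × 0.3 × 0.7) = 2.5 percentage points against a 3-point target.
- **Benefit.** Nothing in the protocol shows that district or volume predicts perinatal mortality. Facility-level pre-trial volumes are implied by a mean and a CV, not documented.
- **Baseline mortality.** If the 0.96 correlation held and a baseline term were fitted, 1 − 0.96² = 8% of the variance would remain for district and volume to act on.

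All of this stands and limits the claim. It does not remove the point. The article names its primary test rather than leaving it to another document, that test has no place for covariates or for the baseline term, and the same article collects data to permit adjustment.

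**Conclusion.** The point holds as a question of precision and of consistency between sections. The stated primary test leaves out two facility-level variables that appear to be available, in a trial where, on the per-1000 reading, 64% to 77% of the variance of an arm difference lies between facilities. The gain from including them is unknown. Across an assumed 10% to 50% explained, the standard error falls by 3% to 21%.

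The result rests on the per-1000 reading, ICC 0.003, 600 births per facility and the assumed share explained. Adjusting for district and volume does not by itself recover 80% power. That figure depends on the baseline-mortality correlation, whose absence from the stated test is a separate and larger matter.

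**What to change.** Before unblinding:

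1. In the analysis paragraph, make the primary comparison a cluster-level regression, or an equivalent model, with arm, three district indicators and log pre-trial deliveries per month. Include alongside them any baseline-mortality term that the Sample Size section implies.
2. Report the unadjusted cluster-corrected chi-square as supportive.
3. In the Randomization section, state whether allocation was restricted. If strata were used, include them in the model.

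**Cost.** The district and volume terms use four degrees of freedom out of about 81 (84 facilities less three arm means), leaving about 77. District is known. Pre-trial volume per facility has to be confirmed as held or obtained. Data collection ended in November 2020 and cleaning or analysis had begun by submission, so this would be a late change to the stated primary test. It must be dated and reported as such, and made while the primary analysis is still blinded, as the Blinding section provides.

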**Figure 1 figure1:**
[figure not shown]
Geographical location of health districts and health facilities under study. LDHF: low-dose, high-frequency; MNCH: maternal neonatal and child health.

**Figure 2 figure2:**
[figure not shown]
Flow chart of community health services clusters recruitment and follow-up. CSCOM: Centre de Santé Communautaire; LDHF: low-dose, high-frequency; MNCH: maternal neonatal and child health.

### Trial Participants and Units of Randomization (Clusters)

The group of facility-based health workers and community health workers within the 4 health districts of the Koulikoro region within each facility (unity of randomization) are eligible to enter the trial. Eligible facilities are those that provide basic obstetric care and have at least one facility-based health care provider trained in AMTSL, ENC, and PNC. The eligibility assessment of facilities was made possible through the data collected during the baseline facility assessment conducted in December 2016.

Facilities within the 4 health districts of the Koulikoro region that did not provide basic obstetric care or those who did not have any health workers who received training in maternal and neonatal health care providers in AMTSL, ENC, and PNC have been excluded. Rural maternities were not eligible, as they are not included in the national audit policy.

### Intervention Strategy

The intervention uses a problem-based learning approach that uses the information emerging from the implementation of maternal and newborn audits to improve health worker skills training. This training is delivered by a study-trained facilitator, employed by Mali’s Ministry of Public Health and Hygiene, that attends and provides feedback during the audit meeting, followed by an immediate (next day) one-day in-service case-based focused training [8,13,14]. Specifically, each training cycle starts with the implementation of a maternal and neonatal morbidity and mortality audit, during which the trainer identifies gaps in knowledge and skills. This is followed by on-site LDHF hands-on training of maternal and neonatal health care providers on the skills and competency gaps highlighted by the audits. The training sessions also include direct observation of care, supervision, and use of simulations. In addition, community health workers are also trained when issues identified during the audit are related to their practice, such as in the identification of danger signs in the community or timely referral to the facility.

We hypothesize that the provision of on-site case-based LDHF hands-on training of maternal and neonatal health care providers, focused on gaps identified through clinical audits, will improve quality of care, thus decreasing adverse events during labor and the immediate postpartum and perinatal period in facility births, in comparison to traditional off-site generic training. The training of community health workers will improve community management via identification of danger signs and timely referral during pregnancy, labor, and the postnatal period (Figure 3). Ultimately, the aim of the intervention is to address key barriers to improving maternal and perinatal health by focusing on increasing the capacity of maternal and neonatal health care providers along with improving the recognition of danger signs and referral during the natal and postnatal period by community health workers.

**Figure 3 figure3:**
[figure not shown]
The intervention model. LDHF: low-dose, high-frequency.

### Study Arms

#### Overview

This study is a three-arm cluster randomized controlled trial including one control and two intervention arms with a gradual increase in the intervention components.

MNCH refresher training and follow-up: the control arm will consist of standard MNCH refresher training delivered in the classroom using multi-method classroom training delivered as part of the larger Canadian Red Cross and Malian Red Cross project. For these training sessions, two maternal and neonatal health care providers from each facility randomized to the control study arm received 10-day classroom training on AMTSL, ENC, PNC, and integrated community case management of childhood illnesses.Audit and feedback with LDHF hands-on training and 6 months follow-up: the first intervention arm will include 28 facilities in which mortality and morbidity audits will be implemented by the study team, followed by one day of case-based focused LDHF hands-on training biweekly for 6 months.MNCH refresher training followed by audit and feedback combined with LDHF hands-on training and 6-month follow-up: the second intervention arm will include 28 facilities that will benefit from MNCH refresher training, in addition to mortality and morbidity audits implemented by the study team, followed by one day of case-based focused LDHF hands-on training biweekly for 6 months.

#### Consent to Participate

Written consent will be obtained from mothers or fathers of newborns at the follow-up household visit and for verbal autopsy. If the mother is not able to give consent, her husband or other adult family member will be requested to give consent to participate in the study. If the respondent cannot read, the consent statement will be read to them, and a thumb impression by the respondent in place of a signature will signify consent. The data collector will explain the risks and benefits to potential enrollees before conducting the verbal autopsy and administering the household questionnaire in the intervention and control clusters. Participants will be informed that they have the right to withdraw from the study at any time and that there are no penalties from doing this, and this will not in any way affect their ability to receive any health care services.

#### Ethical Approval and Protocol Registration

Ethical approval was obtained from the Sickkids Research Ethics Committee (Research Ethics Board number 1000060635) and from the University of Bamako’s Faculty of Medicine Ethics Committee. The project was registered at ClinicalTrials.gov (NCT03656237).

### Process of the Intervention Implementation

#### Audit and Feedback

An audit committee comprising a health facility manager, basic obstetric and neonatal care providers, and district or regional health department representatives will be formed in each facility, following the guidelines developed by Mali’s Ministry of Public Health and Hygiene. The health facility representative designated by the audit committee will be responsible for audit support, including providing medical records and supporting documentation to the audit committee, assisting in the development of the process, procedural walkthroughs, and responding to various inquiries to assist the committee with the development and documentation of the audits.

#### Low-Dose, High-frequency Training

Mali’s Ministry of Public Health and Hygiene’s 10 senior physicians, with gynecological or obstetrical background, will be trained on the implementation of the intervention and will support implementation of the audits, facilitate the process and discussions, and during the audit meeting, identify key knowledge gap areas for the subsequent on-site case-based focused LDHF hands-on training, mentoring, and supervision of MNCH care providers. In this regard, the intervention trainers will stay at the health facility for one consecutive day to implement case-based focused LDHF hands-on training to the facility staff involved in basic obstetric and neonatal care and to community health workers linked to each facility when appropriate, as described above. The training modules will be based on recommendations from the clinical audit and focus on strengthening the core competencies identified by the audit committee as the cause of death or complications in the patient. The trainers will also observe health care providers during service delivery and postnatal care and will use direct observation skills checklist to record identified gaps in clinical skills and knowledge and will assist the health care provider in implementing national service delivery standards and guidelines. The audits will be implemented following the Ministry of Public Health and Hygiene guidelines and will serve as a platform for the identification of cases for case-based, focused LDHF hands-on training. Data from the partographs and facility birth registers will be used to identify the case to be audited. Once identified, audit cases will be anonymized and summarized by the health facility representative. The case summaries will be discussed in detail, identifying causes of death or near miss, perinatal or maternal complications, and assessing the quality of care provided. The findings will be evaluated against existing service delivery standards and protocols. In addition, external factors that adversely affect patient outcomes, such as delayed recognition of danger signs during pregnancy or labor, delayed referrals, and delayed recognition of danger signs during the perinatal period, will be identified during the audit for community health worker training at the corresponding facility. Audit information is the basis for identifying knowledge or case management gaps among health care providers, knowledge-to-action gaps, and training requirements. The summary of each audited case will have a structured section in which the trainer will document action points for training and managerial support, and these will also be recorded in the minutes of the audit committee meeting.

### Research Questions

This cluster randomized trial aims to assess whether LDHF hands-on training, informed by maternal and neonatal mortality audits in routine clinical settings, reduces perinatal mortality. Secondary objectives include estimating the effectiveness of the intervention in improving maternal and neonatal care practices among health workers and the comparative cost-effectiveness of the case-based focused LDHF hands-on training, compared with traditional training.

### Primary Outcome

The perinatal mortality rate per 1000 live births occurring in each facility and the corresponding catchment area for the births that had taken place in the facility will be used to assess the effectiveness of the intervention. It is defined as the sum of *fetal deaths* (stillbirth), defined as the death of a fetus weighing 500 g or more, or of 22 weeks of gestation or more, occurring in health facilities, and *early neonatal death*, namely, the death of a live born within the first 7 days of life occurring in the facility or in the community. As health facility studies are not an appropriate source of data for calculating perinatal mortality incidence [24] unless all babies are born and stayed in a health facility for 7 days, the data on perinatal mortality will be extracted from both facility-level data and household survey questionnaires.

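### The primary outcome counts stillbirths but is expressed per live births, so it is a ratio and not the proportion of births that the planned chi-square and the sample size use; the numerical effect is small

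*Protocol article*

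**What the plan says.** All references are to the protocol article.

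- **Primary Outcome, denominator:** "The perinatal mortality rate per 1000 live births occurring in each facility and the corresponding catchment area".
- **Primary Outcome, numerator:** the sum of two components. The first is stillbirth, "defined as the death of a fetus weighing 500 g or more, or of 22 weeks of gestation or more, occurring in health facilities". The second is early neonatal death, "the death of a live born within the first 7 days of life occurring in the facility or in the community".
- **Results, analysis paragraph:** an "aggregate cluster-level analysis comparing the proportion between treatment arms", followed by "We will compare differences in the proportion of perinatal mortality between intervention and control groups using a chi-square statistic" that is adjusted for clustering through the intraclass correlation coefficient. No denominator is named.
- **Sample Size:** the cluster size is given as 600 births, but the effect is stated as a "reduction in the perinatal mortality rate from 30% to 27% live births".
- **Secondary Outcomes:** live births are the base for most newborn-care items, and deliveries for referral because of postpartum hemorrhage. The authors therefore do use different denominators for different outcomes.
- **Data Collection Methods, Health Facility Data:** records are extracted for all facility births.

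**The concern.** A stillborn baby is in the numerator but cannot be in a denominator of live births. A chi-square on proportions requires every event to be one of the n units, so that events plus non-events equal n. With live births as n, the non-event count (live births minus all perinatal deaths) is too small by the number of stillbirths, and the binomial variance and its intraclass-correlation inflation do not formally apply.

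The denominator also depends slightly on the treatment effect, because each prevented stillbirth adds a live birth.

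This is the sole primary outcome, and it also supplies the effect measure for the economic evaluation. With live births in one section, births in another and an unnamed base for the test, two analysts could follow the text and report different rates, and a reader could not tell which base had been used.

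**Working it through.** **Inputs.** From Sample Size: 28 clusters per arm, 600 births per cluster, alpha 5%, intracluster correlation 0.003, coefficient of variation of cluster size 0.9, correlation with baseline 0.96, rates 30 and 27. Assumptions: the test is two-sided (not stated); the rates are per 1000, although printed as per cent; the stillbirth share s of perinatal deaths is one third to two thirds (the article gives no figure for the study facilities).

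**Step 1: the plan's own power.**
- Design effect = 1 + ((0.9² + 1) × 600 − 1) × 0.003 = 4.255.
- Baseline adjustment = 1 − 0.96² = 0.0784. Product = 0.3336.
- 0.030 against 0.027 needs 48,292 births per arm under independence. Clusters needed = 48,292 × 0.3336 / 600 = 26.85, against 28 available.
- Effective size per arm n = 28 × 600 / 0.3336 = 50,361.
- Power = Φ{[|p₁ − p₂| − 1.96 √(2p̄(1 − p̄)/n)] / √[(p₁(1 − p₁) + p₂(1 − p₂))/n]} = 81.6%.

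The stated 80% is reproduced when the rates are treated as binomial proportions of births. This does not show which base the planning rates came from.

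**Step 2: the table on live births.** Take 1000 live births and 30 perinatal deaths, half of them stillborn. There are 15 stillbirths, 15 early neonatal deaths, 1015 total births and 1000 − 15 = 985 survivors. A table with n = 1000 shows 1000 − 30 = 970 survivors, short by the 15 stillbirths.

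**Step 3: converting the rates.** If R is perinatal deaths per live birth, the proportion of total births is p = R / (1 + sR).

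| s | Per 1000 total births, R = 0.030 | R = 0.027 | Overstatement on live births (sR) | Risk ratio |
|---|---|---|---|---|
| 1/3 | 29.70 | 26.76 | 1.0%, 0.9% | 0.901 |
| 1/2 | 29.56 | 26.64 | 1.5%, 1.4% | 0.901 |
| 2/3 | 29.41 | 26.52 | 2.0%, 1.8% | 0.902 |

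On live births the risk ratio is 27/30 = 0.900.

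**Step 4: the test statistic.** Take 16,800 total births per arm. Live births are 16,800 / (1 + sR), and deaths are R times live births. The pooled two-sample z, before any clustering adjustment, is:

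| s | z, n = live births | z, n = total births | Change | Live births, intervention against control |
|---|---|---|---|---|
| 1/3 | 1.645 | 1.629 | −1.0% | +0.10% |
| 1/2 | 1.641 | 1.617 | −1.4% | +0.15% |
| 2/3 | 1.637 | 1.606 | −1.9% | +0.20% |

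The clustering adjustment would scale both columns by nearly the same factor, so the relative change should carry over. The last column is the treatment-driven shift in the denominator.

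**Step 5: power on total births.** Putting the Step 3 proportions into the Step 1 formula gives 80.5%, 80.0% and 79.4% for s = 1/3, 1/2 and 2/3, if the planning rates were per live births. If they were already per total births, power stays at 81.6%.

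**The case against.** The strongest reply is that live births is loose wording and that births are the working unit throughout. All facility deliveries are included, data are extracted for all facility births, the trial is sized in births, and the analysis paragraph names no denominator. Nothing in the article sets out a table with live births as n. On that reading the analysts would have used total births anyway. This is plausible, but it is an inference: the one place that defines the primary outcome states live births, and no section corrects it.

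The reply also notes that deaths per live birth is a coherent quantity, and that a comparison of cluster-level summaries does not need events to belong to the denominator. Both points stand. The conflict is with the chi-square on proportions, which does need this.

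A reader might go further and infer that the test cannot be carried out, that the primary estimate is invalid, or that the moving denominator biases the comparison. The article's figures do not support any of these. The test can be computed and is a slightly misspecified approximation; the risk ratio moves by 0.001-0.002; and the arms' live-birth counts differ by 0.1-0.2% under the planned effect. Nor can the Sample Size phrase show which base was intended, because it also prints per cent where only per 1000 reproduces the power. That is a separate error.

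**Conclusion.** The definition is wrong as written. A ratio to live births, with stillbirths counted, is paired with a test for proportions and a sample size in births, and the text does not reconcile them. This is not detail left to an analysis plan, because the article states a denominator and that denominator conflicts with its own test.

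The consequence is small: about 1-2% on each arm's rate, 0.900 to about 0.901-0.902 on the risk ratio, and about 1-2% on the test statistic, with live births giving the slightly larger value. At the upper end, only a result with a total-births z between 1.96 × 0.981 = 1.92 and 1.96 would cross the two-sided 5% threshold because of the choice of base. Power stays within about one point of the stated 80% in every case in Step 5.

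These sizes rest on reading the planning rates as per 1000 and on the assumed stillbirth share. The existence of the mismatch rests on neither.

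**What to change.** - **Primary Outcome:** define the rate per 1000 total births in study facilities, where total births are live births plus stillbirths meeting the protocol's own weight or gestation criterion.
- **Sample Size:** state the planning rates per 1000 total births and say that the 600 per cluster are total births. If the source rates were per live births, convert them with p = R / (1 + sR) and give the share used.
- **Results, analysis paragraph:** name total births as n for the cluster proportions and for the adjusted chi-square.
- **Live births:** keep them as the base only for early neonatal death, if reported separately, and for the newborn-care outcomes.

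The cost is wording. Extraction covers all facility births, so both counts should already be available and no new data are needed. Data collection is complete and cleaning or analysis had begun when the article was submitted, so the change should be dated and recorded as a clarification, made while the primary analysis is still blinded to allocation if possible. Reporting stillbirth and live-birth counts by arm would let readers compute either rate.
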